# Comparison of Spinal Cord Stimulation vs. Dorsal Root Ganglion Stimulation vs. Association of Both in Patients with Refractory Chronic Back and/or Lower Limb Neuropathic Pain: An International, Prospective, Randomized, Double-Blinded, Crossover Trial (BOOST-DRG Study)

**DOI:** 10.3390/medicina58010007

**Published:** 2021-12-21

**Keywords:** neurostimulation, burst, leg pain, refractory pain, failed back surgery syndrome, hybrid stimulation, energy consumption

## Abstract

While spinal cord stimulation (SCS) is a well-established therapy to address refractory persistent spinal pain syndrome after spinal surgery (PSPS-T2), its lack of spatial selectivity and reported discomfort due to positional effects can be considered as significant limitations. As alternatives, new waveforms, such as burst stimulation and different spatial neural targets, such as dorsal root ganglion stimulation (DRGS), have shown promising results. Comparisons between DRGS and standard SCS, or their combination, have never been studied on the same patients. “BOOST DRG” is the first prospective, randomized, double-blinded, crossover study to compare SCS vs. DRGS vs. SCS+DRGS. Sixty-six PSPS-T2 patients will be recruited internationally in three centers. Before crossing over, patients will receive each stimulation modality for 1 month, using tonic conventional stimulation. After 3 months, stimulation will consist in switching to burst for 1 month, and patients will choose which modality/waveform they receive and will then be reassessed at 6 and 12 months. In addition to our primary outcome based on pain rating, this study is designed to assess quality of life, functional disability, psychological distress, pain surface coverage, global impression of change, medication quantification, adverse events, brain functional imaging and electroencephalography, with the objective being to provide a multidimensional insight based on composite pain assessment.

## 1. Introduction

Spinal cord stimulation (SCS) is a well-established therapy to alleviate severe intractable neuropathic pain [1,2,3,4,5,6,7] by improving pain control and quality of life [8,9] in patients with failed back surgery syndrome (FBSS) or persistent spinal pain syndrome type 2 (PSPS-T2) [10]. Using this reversible treatment option, the prerequisite to address pain with conventional therapy modality is to obtain appropriate coverage of the painful area, by inducing paresthesia on corresponding painful territories [1,8,11]. Despite its effectiveness, SCS has some limitations.

First, pauci-discriminative stimulation of billions of sensory epicritic fibers of the dorsal columns using electrical impulses makes it very complex for SCS to be selective in terms of pain coverage for patients [11]. This lack of selectivity, associated with the type of implanted lead, its positioning, its properties, patient variability and the challenge to provide adequate spatial and temporal neural targeting using electrical source-specific capabilities, can lead, on the one hand, to feel paresthesia in a non-painful area and, on the other hand, to not be able to cover decisive painful body regions and/or pain trigger(s), particularly in focal distal pain distribution, as in foot and groin pain [12]. As described by Holsheimer et al. [13], lead positioning can dramatically impact paresthesia coverage and energy consumption. New available paresthesia-free waveforms, such as burst, high frequency or high dose, appear to limit this problem by suppressing patient perception of the therapy [14,15,16,17,18,19]. However, they might also result in significantly higher energy consumption, requiring more frequent recharges, or lead to premature battery replacement. Third, a decrease/loss of effectiveness may occur over time [8] due to neural plasticity. This might explain why, up until now, physicians have been obsessively focusing on pain coverage, expending considerable energy to blur nociceptive signals by stimulating long sensory fibers with various SCS spatial programming strategies [4], rather than attempting to stimulate other potential pain generators. One major target appears to be located at the dorsal root ganglion (DRG) level and plays a crucial role in pain generation [20,21]. To validate this hypothesis, medical device and neuromodulation industries have developed DRG stimulation (DRGS) [22]. DRGS appears to be a promising technology for patients suffering from refractory chronic neuropathic pain, and particularly focal pain, since it operates more selectively on the nervous system [22,23,24,25,26,27,28]. Furthermore, DRGS could have an advantage over SCS by processing less positional sensitivity, possessing more stability and superior electrical efficiency in terms of energy consumption. Due to its proximity and lack of cerebro-spinal fluid (CSF), it requires far less amplitude to deliver therapy to the appropriate neural target [13,29]. In a recent high-quality prospective, multicenter, randomized comparative trial conducted on 152 subjects implanted with either an SCS or a DRG stimulation system, Deer et al. [24] reported that DRGS leads to a significantly higher rate of treatment success (≥50% pain relief) compared with conventional SCS (81.2% vs. 56.7%, respectively) in patients with complex regional pain syndrome (CRPS) and/or causalgia. The authors also reported that, using DRGS, pain relief was maintained through 12 months of follow-up and was greater than with SCS. However, in this study, SCS and DRGS were assessed in two distinct groups of CRPS patients, between whom comparison was not possible. Some might not have responded to SCS or DRGS due to their baseline latent confounding variables rather than therapy efficacy variability. Furthermore, synergy between SCS and DRGS working simultaneously on the same patient might catalyze therapy outcome by optimizing spatial and temporal neural tissue targeting, pain coverage (i.e., selectivity), pain relief, cortical perception and, ultimately, electrical consumption. This has never been documented so far.

In parallel with neural spatial targeting improvements, new available waveforms including burst paradigms have changed the modulation of the temporal resolution of the signal, allowing for “paresthesia-free” stimulation [30,31]. Recent clinical trials have provided evidence of burst-SCS efficacy in PSPS-T2 patients [32,33,34,35]. However, to date, only animal studies have demonstrated the effectiveness of burst applied to DRG stimulation [36,37]. The opportunity to apply burst waveform to DRG could help to refine the design of the next generation of internal pulse generators (IPGs) and to explore new mechanisms of action. To our knowledge, DRGS combined with burst has yet to be reported in humans.

In a recent review, Linderoth and Foreman [38] presented the current state of knowledge regarding conventional SCS mechanisms of action, by indicating that gamma-aminobutyric acid (GABA) release and GABA-B receptors are pivotal in suppressing glutamate release and consequently relieve pain [39,40,41,42]. Other animal studies have reported that cholinergic activation can enhance SCS pain relief [43,44]. Similarly, release of neurotransmitters such as adenosine, serotonin and noradrenaline by SCS could contribute to pain relief [43,45,46]. Recent studies have reported that 50% of the effects of conventional SCS in neuropathic pain imply supraspinal circuitry [45,47]. Assuming spinal and supraspinal activation during SCS or DRGS applied in an animal model [47], a recent systematic review synthesizes current literature on the supraspinal mechanisms of action underlying the pain-relieving effect of SCS and DRGS in animal and human studies [46]. Through 54 studies, Goudman et al. [46] reported that three main supraspinal hypotheses indicate modulation of the descending nociceptive inhibitory pathways, followed by modulation of the ascending medial and lateral pathways. The difference, in terms of mechanisms of action, between tonic conventional stimulation (TCS) and burst stimulation could be due to the more selective modulation of the medial pain pathway provided by burst stimulation, as evidenced on metabolic activation of the dorsal anterior cingulated cortex on a limited number of patients [48]. Moreover, TCS significantly increases the spontaneous activity of neurons in the gracile nucleus, which are known to project to the primary somatosensory cortex in the brain. Increased spontaneous activation of the spinal nucleus might account for the sensation of paresthesia that typically occurs during TCS, but not burst stimulation [49]. Combining electroencephalography (EEG) and functional magnetic resonance imaging (fMRI) to test these hypotheses, we gain insight on supraspinal mechanisms of action of SCS and DRGS, including not only tonic conventional stimulation (TCS), but also burst stimulation modalities.

To address these challenges, we designed a randomized controlled trial (RCT) with a 3-month crossover design, where SCS, DRGS or SCS+DRGS (DUAL) will be proposed to a single patient presenting with refractory chronic lower limb neuropathic pain (e.g., CRPS, diabetic foot peripheral neuropathy, foot and ankle peripheral neuropathy, radicular pain associated with PSPS-T2) and/or documented neuropathic refractory back pain. After the crossover period, all patients will be switched to burst waveform with 1-month follow-up, and at 4-month follow-up, they will be asked to choose SCS, DRGS or SCS+DRGS with tonic conventional or burst waveform.

### Aims and Objectives

The BOOST DRG study is a randomized, controlled trial comparing the efficacy of SCS vs. DRGS vs. combination of SCS+DRGS (DUAL) and TCS vs. burst in a crossover design in patients with chronic lower limb neuropathic pain and/or neuropathic back pain.

The primary objective of this study is to compare the efficacy of SCS vs. DRGS vs. DUAL on global pain relief in patients with chronic lower limb neuropathic pain and/or neuropathic back pain.

Secondary objectives are to compare pain intensity, pain surface and paresthesia coverage surface to assess positional or postural effects on paresthesia, to compare changes in quality of life, functional disability and psychological state, to assess patient satisfaction and, finally, to compare the effects of stimulation modalities on brain imaging based on fMRI and EEG. Using this study data, we will extract baseline factors associated with long-term stimulation efficacy. These predictors will be included in a predictive model.

## 2. Materials and Methods

This protocol is reported in accordance with the SPIRIT 2013 guidelines for protocols of clinical trials [50].

### 2.1. Design and Setting

The BOOST DRG study is divided into two phases.

Phase A (Pilot study) is a randomized, double-blinded, crossover, six-arm study evaluating the feasibility and comparing the efficacy of three stimulation modalities: SCS, DRGS and DUAL (SCS+DRGS) on 12 patients during 3-month follow-up, which will be conducted only in Poitiers University Hospital (France). According to the phase A results, in terms of feasibility and safety, a second phase is planned, following the same design and including a larger sample of patients, internationally, to take into account the variability of practices.

Phase B (Main study) is a prospective, multicentric, randomized, double-blinded, crossover, six-arm study comparing the efficacy of three stimulation modalities: SCS, DRGS and DUAL stimulation (SCS+DRGS) on 54 patients, conducted in the Poitiers University Hospital (France), the Colmar Louis Pasteur Hospital (France) and in Genève Tower Hospital Pain Clinic/Lausanne University Hospital (Switzerland).

Phase A and phase B have the same design. Patients will be implanted with the Octrode^TM^ contact percutaneous lead for SCS and one or several Quattrode^TM^ lead(s) for the DRGS, enabling use of the three different stimulation modalities in the same patient. The leads will be connected to a single external pulse generator. Patients will be randomized in 6 different arms in a 1:1:1:1:1:1 ratio: SCS alone, DRGS alone and DUAL stimulation. During the 3-month crossover period, patients will be under the tonic conventional stimulation (TCS) waveform, whatever the stimulation modality. Each stimulation modality will be administered for 1 month. Patients will be assessed at the end of each stimulation modality period, corresponding to the 1-month, 2-month and 3-month follow-up visits. At the end of the crossover period, stimulation modality will not be changed and will be switched to the burst waveform for 1 month. Patients will be assessed at the end of this 1-month period, corresponding to the study’s 4-month follow-up visit. Patients will then decide which stimulation modality and waveform they prefer and will be assessed at 6 months and 12 months.

Patient flow and the study design are presented in Table 1 and Figure 1, respectively.

### 2.2. Patient Selection

The study population comprises patients suffering from chronic lower limb neuropathic pain and/or neuropathic back pain. A patient must meet all inclusion criteria and none of the non-inclusion criteria and the exclusion criteria to be eligible for the study.

#### 2.2.1. Inclusion Criteria

The patient, aged between 18 and 80 years old, presents with refractory chronic lower limbs neuropathic pain or/and neuropathic back pain for at least 6 months, with VAS ≥ 5/10. The patient’s symptoms are stable for at least 30 days. Pain medication dosage(s) are stable for at least 30 days and the patient is refractory to other treatment modalities (e.g., medication, psychological therapies, pain interventions, surgery). The patient is eligible for SCS after a pre-implantation assessment by a multidisciplinary team, as described by the French National Authority for Health (Haute Autorité de Santé (HAS)). The patient is covered by French national health insurance. The patient understands and accepts the constraints of the study and has given written consent to the study after receiving clear and complete information.

#### 2.2.2. Non-Inclusion Criteria

The patient has a coagulation disorder, had corticosteroid therapy within the past 30 days, had radiofrequency therapy within the past 3 months, was diagnosed with cancer in the past 2 years or had surgery within the past 6 months. The patient is or has been treated with SCS, subcutaneous or peripheral nerve stimulation, an intrathecal drug delivery system. The patient requires closer protection, i.e., minors, pregnant women, nursing mothers, subjects deprived of their freedom by a court or administrative decision, subjects admitted to a health or social welfare establishment, major subjects under legal protection and, finally, patients in an emergency setting. The patient participates in any interventional study on health product or any study able to interfere with the current study endpoints. Women of childbearing potential not using an effective contraception are not expected to be included in this study. For Poitiers University Hospital only, patients who have magnetic brain imaging (MRI) contraindications will not be included.

#### 2.2.3. Exclusion Criteria

The patient is unable to appropriately use stimulation equipment, the patient has failure of the trial phase, defined as pain reduction <50% between the inclusion visit and 7 days after lead implantation or the patient presents with any medical condition judged as relevant/significant by the investigator.

### 2.3. Interventions

Subjects who meet all the inclusion criteria and none of the non-inclusion or exclusion criteria will be implanted with the Octrode^TM^ contact percutaneous lead for SCS and one or several Quattrode^TM^ lead(s) for the DRGS, depending on the pain (bi)lateralization and the pain topography (Figure 2).

The following implantation procedure describes the various steps of the surgery until final implantation of the lead. The procedure length is about 90 min.

#### 2.3.1. Phase 1: Lead Implantation

The lead positioning under awake anesthesia will allow for patients to be tested intra-operatively in order to determine the anatomical sweet spot and the optimal paresthesia coverage, according to patient-specific pain distribution. Preliminary electrophysiological testing will be performed on leads and percutaneous leads will then be navigated longitudinally through the following.

The epidural space, to determine the best vertebral level and implantation site, addressing the “sweet spot” location (an anatomical area located within the dorsal column (DC) of the spinal cord, able to provide significant paresthesia generation in the adequate dermatome, if electrically stimulated) [51], during an initial phase of intra-operative testing of the percutaneous SCS lead.

The foramen, using a trans-grade approach [52], to target the DRG(s) and determine the best location of implantation in terms of vertebral level, foramen level and final lead positioning.

Epidural fat and scar tissue formation could play a substantial role in the energy delivered from the IPG to dorsal column or DRG. This will be explored by following impedance throughout the study and will be taken into account as a potential limitation. To reflect daily practice, impedance will be measured at each contact level according to the user’s manual (between 200 and 3000 Ω) in this clinical study. In case of impedance higher than 3000 Ω, the contact will be automatically deactivated. In this case, we will activate contacts with whom the patient will experience the best pain relief. Some TCS patterns will be tested thanks to the patient’s cooperation, by using various predetermined combinations to achieve good pain coverage and validate the “sweet-spot” location. This will be facilitated by an integrated operating room including several of the new computer-assisted and imaging-assisted technologies (multiple splitable screens with wall live projection, full HD camera filming the patient and C-arm monitor, HF microphones and earphones enhancing surgeon/patient per-operative crosstalk, etc.) designing an operative theater [53].

After completion of lead programming testing, the leads will be permanently implanted and secured with appropriate anchoring, at the final vertebral level. Very specific attention will be given to the DRG(s) anchorage. The rest of the procedure will be performed as already described in our previous published works [31,54].

Potential lead migration should be documented by imaging in case the patient experiences inadequate pain relief and/or for coverage after initial positive outcome. In case of lead displacement, documented by X-ray, a revision surgery will be recommended to check hardware dysfunction, including lead migration or fracture. This complication will be reported as an adverse event. Pain rating and outcomes will be analyzed taking the adverse event into account.

#### 2.3.2. Phase 2: SCS+DRGS Trial Phase

During the trial phase, both SCS and DRGS will be used separately and/or simultaneously. The trial will be performed for a period of 7 days to assess the benefits of stimulation according to HAS guidelines prior to definitive implantation of the IPG. IPG implantation will be based on the following criterion: at least 50% reduction of pain assessed with a visual analogic scale (VAS).

Following surgical implantation of the leads, after 24 h of strict bed rest to avoid secondary early lead displacement, lead programming will be performed according to the TCS by testing a series of programming combinations designed to obtain coverage of the painful territory.

In case of SCS/DRGS trial failure, the leads will be removed, and the patient will be managed according to standard practice (including another assessment by the pain physician to define a nonsurgical solution). If the patient is explanted, he/she will be excluded from the study.

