### 2.5. Clinical Assessments

Randomization is carried out at the IPG implantation visit. Subjects are assessed prior to randomization, during the inclusion visit and the lead implantation visit, and at 1-month, 2-month, 3-month, 4-month, 6-month and 12-month follow-up visits. Assessments are performed by appropriately trained and delegated study staff independently from industry. Details about which information will be collected at each visit can be found in Table 1.

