Two interim analyses are planned. The first interim analysis will be conducted on data from the first 12 patients included (after the “Tonic” crossover period). In this first interim analysis, we will analyze only the safety criteria, the objective being to assess study feasibility. The second interim analysis will be conducted on data from the first 33 patients included (after the “Tonic” crossover period) and will be exclusively descriptive. No hypothesis testing will be conducted. This analysis will be conducted on primary and secondary outcomes. As the study is of long duration (3.5 years), we decided to include a second interim analysis to communicate the results to the scientific community by clearly indicating that this is an interim analysis and that the final analysis will be conducted on the total sample of 66 patients. This may lead to other projects and accelerate the progress of research on the stimulation of several anatomical targets. These results will have no impact on study completion. The final analysis on 66 patients will be considered for the report and the publications.

Only data from the crossover period will be used in the interim analysis. The statistical methods used in this interim analysis will be similar to the methods used in final analysis described above. No adjustment of the final analysis *p*-values will be conducted as the interim analysis results do not influence in any way the course or the conduct of the study.

A significance level of 0.05 will be considered in this study (after taking into account multiple testing corrections) and all tests will be two-sided.

All the analyses will be conducted based on an Intention-To-Treat (ITT) principle using complete cases. No missing data imputation will be conducted. An initial safety analysis will be conducted on the first 12 patients to assess the initial safety of implementing patients with both DRG and SCS stimulations. A final safety analysis will be conducted on the 66 patients. Frequencies of adverse events and deviations from protocol will be compared between the treatments following an ITT analysis.

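### Read as written, the phase A go-ahead look leaves out lead implantation, the 7-day trial and explantation, although it is meant to judge the safety and feasibility of implanting both systems

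*Protocol article*

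**What the plan says.** The order of events matters here.

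- **Implantation.** Under Section 2.3, eligible patients "will be implanted with the Octrode^TM^ contact percutaneous lead for SCS and one or several Quattrode^TM^ lead(s) for the DRGS".
- **Trial phase.** Section 2.2.3 lists as an exclusion criterion "failure of the trial phase, defined as pain reduction <50% between the inclusion visit and 7 days after lead implantation". This criterion can only act after surgery. Section 2.3.2 gives the consequence: "In case of SCS/DRGS trial failure, the leads will be removed, and the patient will be managed according to standard practice", followed by "If the patient is explanted, he/she will be excluded from the study".
- **Randomization.** Section 2.5: "Randomization is carried out at the IPG implantation visit". It therefore follows a successful trial phase.
- **Go-ahead.** Section 2.1 describes phase A as a study "on 12 patients during 3-month follow-up" and continues: "According to the phase A results, in terms of feasibility and safety, a second phase is planned".
- **The look itself.** Section 2.7.2 places the first interim analysis after the tonic crossover in the first 12 included patients. It is limited to safety criteria, with feasibility as its purpose. A later paragraph confines the interim analysis to crossover data. Further on the section adds: "An initial safety analysis will be conducted on the first 12 patients". The stated aim there is the safety of having both DRG and SCS systems in one patient.
- **Safety window.** Section 2.5.2 evaluates adverse events, serious adverse events and device deficiencies from inclusion to month 12.

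**The concern.** Exposure to the dual implant begins at lead placement, not at the first month of randomized stimulation. A patient explanted after the 7-day trial has no crossover period, so a look that uses only crossover data contains nothing from that patient. The same rule drops the placement and trial-week events of patients who do continue.

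These are the events that a pilot of a new dual-lead procedure should measure. Section 3.3 itself expects that epidural fibrosis and posterior instrumentation can make the DRG approach very difficult in this population. If the decision to treat 54 more patients rests on crossover months alone, feasibility will tend to look close to complete and early procedural harm will not be counted.

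**Working it through.** **Reproducing the plan's count.** Phase A 12 + phase B 54 = 66, as stated in Section 2.7.2.

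**Tracing one patient who fails the trial.**
1. Leads implanted (2.3): exposed to both systems.
2. Less than 50% pain reduction at 7 days (2.2.3): leads removed, patient leaves the study (2.3.2).
3. No IPG visit, hence no randomization (2.5) and no crossover period.
4. Crossover-only interim (2.7.2): contributes no data.
5. Safety from inclusion (2.5.2): should contribute.

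Steps 4 and 5 cannot both govern the phase A look.

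**Size.** The document gives no trial-failure rate, so the rate f is an assumption, shown over a range. The meaning of the 12 is also open, so both readings are worked.

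*Reading A: the 12 are patients who passed the trial.* Number implanted = 12/(1 − f). Expected number outside the look = 12f/(1 − f). Chance that at least one is outside = 1 − (1 − f)^12.

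*Reading B: the 12 are counted at inclusion, before implantation.* Expected number contributing no crossover data = 12f. Expected number contributing = 12(1 − f).

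| Assumed f | A: implanted | A: outside the look | A: chance of at least one | B: no data | B: contributing |
|---|---|---|---|---|---|
| 5% | 12.6 | 0.6 | 46% | 0.6 | 11.4 |
| 10% | 13.3 | 1.3 | 72% | 1.2 | 10.8 |
| 20% | 15.0 | 3.0 | 93% | 2.4 | 9.6 |
| 30% | 17.1 | 5.1 | 99% | 3.6 | 8.4 |

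Example at 20%: 12/0.80 = 15.0 implanted, 15.0 − 12 = 3.0 outside, and 1 − 0.80^12 = 0.931.

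The gap exists under either reading. Only its form differs: patients outside the denominator (A), or patients inside it with no data (B).

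**The case against.** Four counter-arguments deserve weight.

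*The crossover remark may be about timing only.* Placing the look after the tonic crossover can mean when it happens, not whose data enter. The sentence on the initial safety analysis carries no crossover restriction. The crossover-only sentence follows the text on the second, descriptive interim and may be meant for that one alone. This stands as a possible reading, but the text does not say so, and a go-ahead decision should not depend on which reading is chosen.

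*Safety is already defined from inclusion.* True, and Section 2.3.1 requires lead displacement to be reported as an adverse event. Nothing says that collected events are discarded. A reader might infer that they go unrecorded, or that trial failures are absent from the final safety analysis. The document does not support either inference. Section 2.7.1 speaks of 66 patients to be included and counts possible explants in its 17% dropout allowance, so some explanted patients may well be among the 66. It is true that adverse events are to be compared between treatments by intention to treat, and an unrandomized patient has no place in that comparison. This does not show that such patients are left out of the overall safety report.

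*Trial failure is not implant failure.* It is defined by insufficient pain relief. It would be wrong to describe every missing patient as a failed placement or a device complication.

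*Safety sets belong in the full protocol or analysis plan.* Often so, and the absence of a named set is not the point. The point is that the article states a data restriction that conflicts with its own safety window and with the aim of the look.

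Finally, selecting patients on trial response before randomization is deliberate. It narrows the population but does not bias the randomized efficacy comparison.

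**Conclusion.** The point holds for the phase A go-ahead look. As written, implantation, trial-week and explant events, and all patients who fail the trial, do not inform the decision to start phase B. This contradicts the safety window in Section 2.5.2. At assumed failure rates of 10% to 30%, about 1 to 5 implanted patients fall outside a look of 12 who passed the trial, or about 1 to 4 of 12 included patients supply no data. These figures rest on the assumed rates and on applying the crossover-only sentence to the first interim. If that sentence was meant only for the second interim, what remains is an ambiguity to clear up. No gap in the final safety analysis on 66 is shown, and efficacy is unaffected.

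**What to change.** Reconcile Sections 2.3.2, 2.5.2 and 2.7.2:

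- State that the crossover-only restriction does not apply to the first (safety) interim analysis.
- Base that look on all patients in whom lead implantation was attempted, counting events from implantation and, for those explanted, through explant.
- Report placement success, trial pass rate and explants with that denominator, and let the phase B decision rest on those results.
- In Section 2.3.2, say that an explanted patient is not randomized but is retained in the safety set.

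Efficacy analyses stay on randomized patients, and no clinical rule changes. The cost is wording, plus adverse-event data through explant, which the from-inclusion window already implies. The downside is that phase A safety and feasibility figures may look less favourable.
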